### Outcomes sample

Only patients who are members at UAIHC and who meet the inclusion/exclusion criteria are eligible to enroll in this study. Participation in the study will continue for at least one year after enrollment. It is anticipated that at least 500 patients will consent to participation during the first nine months of the study. Our primary outcome for our main analysis is change in total costs (see the Analysis section below). Using the standard deviation seen in a set of healthcare utilization data from a related group, a sample size of 200 patients should be sufficient to detect a small effect size (Cohen’s d = .20) difference in total costs at a .80 power using an alpha of .05. Therefore, our expected sample size of 500 may also allow for some subgroup analysis. Inclusion criteria: 1) Enrollment in primary care (members) at UAIHC; and, 2) adults ages 18 or older. Exclusion criteria: 1) currently pregnant at time of recruitment; 2) patients who attend the UAIHC clinic as “consultation-only” patients; and, 3) significant cognitive impairment to the extent that the individual is unable to understand the consent and respond to questionnaires.

All new patients will be advised by their primary care physician that they may be eligible to participate in a study to evaluate the effectiveness of the UAHIC. Prior to checkout, patients have an exit session with the University of Arizona (UA) Study Coordinator. During this session (or if necessary, through a follow-up phone call), the Study Coordinator will explain the nature of the study and make a determination of study eligibility, and if appropriate, consent the patient. Patients who joined the UAIHC before study start (July 2013) will also have the opportunity to participate. The study will be explained at their first UAIHC visit after study start.

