### Data Collection

For the outcomes evaluation, data will be collected from patient charts and self-reports at four intervals—baseline (initial clinic visit), and at 3-, 6-, and 12-month follow up periods. Participants will receive a reminder email one week before each data collection due date. Baseline data will be due within one week of enrollment. In the email they will be directed to a secure website where they can access and complete the outcomes data collection instrument. If participants have not entered their data within 3 days of their due date, they will receive another reminder email, and those who have not entered their data within another 3 days of their due date will receive a call from the UA Study Coordinator. Healthcare utilization and cost data from healthcare claims will be obtained from their employer with study participant consent. These data will be collected for one year before and one year after clinic enrollment approximately 3 months after the 12-month follow up period to allow time for all incurred claims to be recorded. De-identified claims data for the comparison groups will be collected for the same period of time with “baseline” being defined by the average start date of study participants.

Because the intervention may change over time as clinic operations start up and mature [21], fidelity monitoring data will be collected monthly from study start for 6 months, then quarterly for 6 months, and then semi-annually. Patient-reported fidelity data will be gathered on a single randomly chosen day of the last week of the data collection month from all patients seen at the UAIHC clinic that day. This day will be selected by the UA research team using a simple computer generated randomization scheme and delivered to the UA Study Coordinator the week before the data collection week. A self-administered patient version of the “How is UAIHC doing?” questionnaire will be used for patients. For clinic personnel, fidelity data will be collected during the last week of each fidelity data collection month using an online self-administered practitioner and staff version of the “How is UAIHC doing?” questionnaire. Data from audits of randomly selected, de-identified patient charts and of administrative records will also be used to assess indicators of model implementation.

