The fifth analysis will focus on the subset of patients for which health insurance claims data are available and will utilize a matched comparison design. Prior to analysis all claims data for each individual (treatment and comparison groups) will be aggregated (by summation) into per health plan member per month (PMPM) totals of paid amounts (the amount paid by the health plan to the practitioner) for each of the following cost categories: total, inpatient, outpatient, emergency room, physician, and pharmaceutical claims. Similarly, the numbers of outpatient visits, hospital stays and emergency department visits will also be aggregated for each individual. The primary outcome will be total cost. Two comparison groups from de-identified claims data will be created—one using simple matching (e.g., by age and gender) and one using propensity scores [49]. After the comparison groups have been selected, simple descriptive analyses will show average PMPM costs and healthcare utilization (including standard deviations and other measures of dispersion) pre- and post- enrollment (or an equivalent date for the comparison groups) by gender, age, baseline diagnosis and by treatment and comparison group. Because cost data tends to be highly skewed, average PMPM costs and healthcare utilization pre/post enrollment, and the change in costs and utilization pre/post between the treatment and each of the comparison groups will be reported as mean differences with confidence intervals calculated using bootstrap methods [83,84]. Because of the number of data points for each patient (e.g., up to 12 PMPM values pre-enrollment and 12 post-enrollment), HLM [80-82] will be used to estimate the pattern of change in healthcare utilization and costs over time, and to explore the determinants of those patterns. Fidelity measures with significant changes over time [24], demographics, participants’ membership level and baseline diagnoses will be included as covariates in these models. Finally, changes in costs between groups will be compared to changes in patients’ CVD risk.

Results for the last two analyses will be reported following the Strengthening the Reporting of Observational Studies in Epidemiology (STROBE) guidelines [85]. For all outcomes, the estimated treatment effects will be reported using their original outcome scale and including confidence intervals.

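### Excluding women pregnant at recruitment while counting all claims in the year on each side of clinic enrollment tilts the pre/post cost change toward savings; the size is small to moderate and rests on assumptions

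*Protocol article*

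**What the plan says.** All references are to the Protocol article.

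- **Who is left out.** Outcomes sample: "Exclusion criteria: 1) currently pregnant at time of recruitment". Nothing bars a woman who gave birth in the preceding year.
- **When that is judged.** New patients: "Prior to checkout, patients have an exit session with the University of Arizona (UA) Study Coordinator". For members who joined before July 2013: "The study will be explained at their first UAIHC visit after study start". For this second group, recruitment can fall well after joining the clinic.
- **Claims window.** Data Collection: "These data will be collected for one year before and one year after clinic enrollment". Health Insurance Claims Data says the same. Table 1 instead words the post-period by study enrollment.
- **What is summed.** Analysis, fifth analysis: "Prior to analysis all claims data for each individual (treatment and comparison groups) will be aggregated" into "total, inpatient, outpatient, emergency room, physician, and pharmaceutical claims". Hospital stays are counted as well. Maternity is not separated anywhere.
- **Status of the outcome.** Outcomes sample: "Our primary outcome for our main analysis is change in total costs". Analysis: "The primary outcome will be total cost". Table 1 marks cost for both a pre/post comparison and a comparison with two matched control groups.
- **Comparison groups.** One is matched on age and gender and one by propensity score, whose variables are not listed. Their baseline is the mean start date of participants. No pregnancy condition at that date is stated.

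**The concern.** The exclusion conditions on a state at one point in time, and that point lies at or near the boundary between the two cost windows. It does not touch deliveries that are already over. It removes nearly all deliveries that would have followed in the next nine months. A delivery brings inpatient, physician and pharmaceutical claims, so the criterion itself produces a step down at enrollment, which is exactly where a clinic effect would be sought.

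At stake are the participants' pre/post change with its bootstrap confidence interval, the inpatient and hospital-stay results, the breakdown by gender and age (where the step is undiluted among women of childbearing age), and the monthly hierarchical model. The between-group change is exposed too if comparison members pregnant at their index date keep their post-year deliveries.

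**Working it through.** **1. The plan's own figure.** Inputs from Outcomes sample: d = 0.20, power 0.80, alpha 0.05 (two-sided assumed). Paired or one-sample formula: n = ((1.96 + 0.8416)/0.20)² = 196.2, so 197 (199 with the t distribution). This agrees with the stated 200. A two-group comparison would need 393 per group. The figure is not affected by this point; it shows that d is best read on the SD of change, which is the scale used in step 5.

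**2. When a delivery can occur.** Assume 38 weeks from conception to term. The pre-year admits deliveries in all 52 weeks. If recruitment coincides with clinic enrollment, the post-year admits them only in the last 52 − 38 = 14 weeks: 14/52 = 0.27, a fall of 73%. Rounding to nine months gives 3/12, a fall of 75%. A simulation with constant conception rates of 0.05-0.15 per woman-year gives post/pre ratios of 0.27-0.28 for eligible women. Without the pregnancy condition the ratio is about 1.0 (0.091 deliveries per woman in each year at a rate of 0.10).

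**3. What weakens it.** With recruitment m weeks after clinic enrollment, deliveries can occur before week m and after week m + 38.

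| Situation | By hand | Simulated post/pre ratio | Fall |
|---|---|---|---|
| Recruited at clinic enrollment | 14/52 = 0.27 | 0.27-0.28 | 72-73% |
| Pregnancies under 6 weeks unrecognised | 20/52 = 0.38 | 0.39-0.40 | about 60% |
| Recruited 3 months later | (13+1)/52 = 0.27 | 0.29 | 71% |
| Recruited 6 months later | 26/52 = 0.50 | 0.53 | 47% |
| Recruited 9 months later | 39/52 = 0.75 | 0.79 | 21% |

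The direction is the same in every row.

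**4. Prenatal claims.** With cost spread evenly over nine months, the average prenatal time inside a 12-month window is (9²/2 + 9 × 3)/12 = 5.625 months, or 62.5%, on each side. Prenatal cost roughly balances, so the net artefact is the delivery cost. If prenatal cost rises toward term, the pre-year holds more of it.

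**5. Size, on assumed inputs.** Artefact per participant-year = share of women of childbearing age × deliveries per such woman-year × paid amount per delivery × 38/52. The document gives none of the first three, nor the SD of change, assumed here at $8,000-20,000.

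| Case | Inputs | Per participant-year | PMPM | d |
|---|---|---|---|---|
| Low | 20%, 3%, $8,000 | $35 | $3 | 0.002-0.004 |
| Middle | 35%, 6%, $15,000 | $230 | $19 | 0.012-0.029 |
| High | 50%, 10%, $20,000 | $731 | $61 | 0.037-0.091 |

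These use the largest fall. In the middle case, 0.35 × 0.06 × 15,000 = $315 of pre-year delivery cost. A 60% fall gives about $190, a 47% fall $148 and a 21% fall $66.

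With no clinic effect, the two-sided false-positive rate of the pre/post test at n = 200 is 1 − Φ(1.96 − d√200) + Φ(−1.96 − d√200): 5% (low), 5-7% (middle) and 8-25% (high).

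Within women of childbearing age the share drops out of the formula. The middle case is then 0.06 × 15,000 × 38/52 = $658 per woman-year, or about $55 PMPM.

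**6. Comparison groups.** A comparison pool with no pregnancy condition has a post/pre delivery ratio near 1.0. Subtracting its change leaves the participants' artefact in the between-group difference. With the same condition at the index date, the artefact largely cancels there, but it remains in the participants' own pre/post change.

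**The case against.** **The effect is small.** This stands. Against the planned d = 0.20, the middle case is 6-14% (0.012/0.20 to 0.029/0.20). Only the high case raises the false-positive rate at n = 200 clearly. Chance also matters: with 30% women of childbearing age and 5 deliveries per 100 a year, 200 participants have 200 × 0.30 × 0.05 = 3 pre-year deliveries against 0.75 post-year at the maximal fall. That difference of 2.25 has a Poisson SD of √3.75 = 1.9.

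**The inputs are assumed.** This stands too. The calculation supposes that participants had an ordinary birth rate in the year before joining. If recent mothers join a fee-based clinic less often, the artefact shrinks; if more often, it grows.

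**Recruitment is not the index date.** This is correct and limits the size. A reader might infer that no participant can be pregnant at the start of the post-window. The protocol does not guarantee that: the window is anchored on clinic enrollment, earlier joiners are recruited later, and no pregnancy test is stated.

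**The matched contrast is the main one, and its details may lie elsewhere.** Table 1 does give the matched comparison as primary, and a condensed article may leave propensity variables and code lists to a fuller document. So the between-group bias is conditional. But age and gender matching as described does not supply the condition, and no matching can repair the participants' own pre/post figure. Baseline diagnoses in the hierarchical model might absorb part of the step; the text does not show that they would, and the bootstrap mean differences are described without such adjustment.

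**Conclusion.** The point holds as a directional artefact produced by three stated rules taken together: the exclusion at recruitment, the symmetric one-year windows, and the sum over all claims. It favours the clinic in total cost, inpatient cost and hospital stays. For the participants' pre/post change this follows from the text. For the between-group change it holds unless the comparison groups meet the same not-pregnant-at-index condition.

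The cost range of about $35-730 per participant-year assumes recruitment at clinic enrollment and is lower for late-recruited members. If Table 1's study-enrollment wording governs the window, the full asymmetry applies to them as well.

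Two stronger readings are not supported. One is that the artefact alone could create the planned effect: even the high case reaches less than half of d = 0.20. The other is that total cost is unfit as the primary outcome: it can stay, provided the comparison pools follow the participants' rule and a maternity-excluded result stands beside it.

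**What to change.** In the fifth analysis:

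1. Exclude from both comparison pools, before matching, members whose claims show pregnancy at the index date, to mirror the participants' exclusion.
2. Report the pre/post and between-group changes in total cost, inpatient cost and hospital stays with pregnancy- and delivery-coded claims removed from both windows in all groups, beside the all-claims total. Base any statement about savings within participants on the maternity-excluded figures.

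Step 1 alone would leave the pre/post change biased, so both are needed. Eligibility of participants does not change.

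The cost is one code list, a few lines of analysis text and one extra set of results, from claims already to be obtained. The downside is that the maternity-excluded figure does not cover all care; the all-claims total beside it still does. Step 1 is also an approximate mirror, because claims may reveal early pregnancies that an eligibility interview misses.

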### Study design

A combination of observational quantitative and qualitative study designs will be used to measure the health and healthcare utilization outcomes of a primary care IM clinical model. Where possible, the clinical and economic impacts seen in this IM model will be compared to data available from one or more comparison groups (see discussion of comparison groups below). When comparison group data are not available for outcomes —e.g., for most of the self-report data and for the medical records data—baseline values for clinic participants will be compared to those measured during and after treatment. Table 1 shows the types of comparisons planned for each outcome data category for the observational study.

**Table 1 T1:** Outcomes measured for the UAIHC

	**Frequency of measurement**	**Pre/post comparisons**	**Comparisons against control group(s)**
Healthcare utilization and costs	One year prior and one year post-study enrollment	X	X^*^
Diet quality	BL, 3, 6, and 12 months	X	X^**^
Exercise	BL, 3, 6, and 12 months	X	X^**^
Patient satisfaction	3, 6, and 12 months	X	X^***^
Self-report health outcomes	BL, 3, 6, and 12 months	X	
• Self-efficacy			
• Stress			
• Sleep quality			
• Pain			
• Fatigue			
• Depression			
• Anxiety			
• Health-related quality of life			
• Well being			
• Work productivity			
• Condition-specific			
• outcomes			
Medical records data	3, 6, and 12 months	X	

BL = baseline (clinic enrollment).

^*^Primary outcome; comparison is to two matched control groups.

^**^Comparison here is to national (and where available statewide) averages from the Center for Disease Control and Prevention’s Behavioral Risk Factor Surveillance System (BRFSS) survey [51].

^***^Comparison here is to national and regional norms using the Consumer Assessment of Healthcare Providers and Systems (CAHPS) Adult Visit Survey 2.0 data [50].

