### Health Insurance Claims Data

Annually, the UA Study Coordinator will create a coded, numeric list of study participants, who are employees or adult dependents of participating employer groups, to send to their health plan. This list will enable the health plan to generate and return a file of otherwise de-identified health claims data. Study participants will be identifiable (a partial waiver of protected health information data was granted by the UA Institutional Review Board) so that healthcare utilization data can be matched to their other study data, and the remainder of the file will be used to generate the matched control groups. The initial data request will cover one year prior and one year after clinic enrollment for study participants, and a comparable 2-year period for non-participants.

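### Table 1 and the text anchor the primary cost window to different dates, and members who joined before July 2013 give directly collected self-report baselines only after clinic care has begun

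*Protocol article*

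**What the plan says.** **Who may join.** The Outcomes sample section of the protocol article admits existing members: "Patients who joined the UAIHC before study start (July 2013) will also have the opportunity to participate". For them, "The study will be explained at their first UAIHC visit after study start". New patients are told of the study by their physician and seen by the study coordinator before checkout, or phoned afterwards.

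**Index date for costs.** The healthcare utilization and costs row of Table 1 (Study design), flagged as the primary outcome, gives the window as "One year prior and one year post-study enrollment". The text uses another date. Data Collection says "These data will be collected for one year before and one year after clinic enrollment", and Health Insurance Claims Data says "The initial data request will cover one year prior and one year after clinic enrollment for study participants". The abstract also speaks of comparison before and after joining the clinic. For the comparison groups, Data Collection takes the average start date of participants as baseline, without saying which start.

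**Baseline for self-report.** The Table 1 footnote reads "BL = baseline (clinic enrollment". Data Collection gives "baseline (initial clinic visit), and at 3-, 6-, and 12-month follow up periods" and adds "Baseline data will be due within one week of enrollment", without saying which enrolment is meant. Outcome measures says that some baseline items are collected directly and others come from the clinic's intake form.

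**Use.** The fourth analysis (Analysis section) compares baseline with 12 months by paired tests in the whole outcomes sample, with health-related quality of life as primary. Table 1 shows no control comparison for these outcomes. The fifth analysis compares claims costs with two matched groups.

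**The concern.** A before/after design depends on the date that separates before from after. For a new patient, clinic and study enrolment nearly coincide, so the loose wording does no harm. For someone who joined before July 2013, they differ by the whole of that person's prior membership.

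Two things follow. First, the primary cost outcome has two index dates, and an analyst could follow either and be within the protocol. Second, the stated self-report baseline cannot be met for any item first asked of an existing member at study entry, because clinic care has by then begun. Where care has already helped, such a baseline hides part of the change. With no control group for these outcomes, nothing in the comparison would reveal it.

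**Working it through.** **1. The plan's own figure.** The Outcomes sample section gives 200 patients for d = 0.20 in total costs, power 0.80, alpha 0.05. Sidedness is not stated; two-sided is assumed. The one-sample or paired form reproduces it:

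n = ((1.960 + 0.842)/0.20)² ≈ 197 (normal), 199 (paired t).

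Power at n = 200 is 80.7% (normal) or 80.4% (t). The figure itself is not in dispute here and serves only as a scale for step 3.

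**2. The two cost anchors for a member with k months of clinic care at study entry (k ≤ 12).**

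| Anchor | Pre-year | Treated months in pre-year |
|---|---|---|
| Clinic enrolment (Data Collection; Health Insurance Claims Data; Table 1 footnote for baseline) | 12 months before joining the clinic | 0 |
| Study enrolment (Table 1 cost row) | 12 months before consent | k |

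Claims are retrieved retrospectively, so the clinic-enrolment window gives an untreated pre-year for earlier members too.

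**3. Size under the study-enrolment anchor only.** Assume a full, constant effect from the first month of membership and an unchanged standard deviation. The share of the effect that remains in the pre/post change for one member is 1 − k/12:

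- k = 3: 75%
- k = 6: 50%
- k = 9: 25%

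If a share f of the sample are earlier members, the average effect is d = 0.20 × (1 − f·k/12). The documents give neither f nor k, so these are assumed ranges:

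| f | k | d | Power at n = 200 | n for 80% |
|---|---|---|---|---|
| 10% | 3 | 0.195 | 78.7% | 207 |
| 10% | 6 | 0.190 | 76.6% | 218 |
| 25% | 6 | 0.175 | 69.7% | 257 |
| 50% | 6 | 0.150 | 56.4% | 349 |
| 50% | 12 | 0.100 | 29.3% | 785 |

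The third row: 0.20 × (1 − 0.25 × 6/12) = 0.20 × 0.875 = 0.175, and 0.175 × √200 − 1.960 = 0.515, giving power 69.7%. Under the clinic-enrolment anchor every row returns to d = 0.20.

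**4. Self-report baseline.** No arithmetic is possible, because the onset of any gain is not given either. For an earlier member there are two routes:

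- *Item collected directly at study entry.* It is measured after k months of care, contrary to both stated definitions of baseline.
- *Item taken from the intake form.* It is a genuine pre-care value, but the clock is then unclear. If follow-up runs from study entry, the 12-month comparison spans 12 + k months. If it runs from joining the clinic, a member with k above 3 has already passed the 3-month assessment.

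The protocol article states no rule for either case.

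**The case against.** The strongest reply is that the cost problem is one table cell. The footnote to the same table, two text sections and the abstract all point to clinic enrolment, and the claims section describes what the health plan is actually asked to supply. On that reading the cost pre-year is clean for everyone. This stands: the cost part is a contradiction to remove, and the dilution in step 3 applies only if the table cell is followed.

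The self-report point can also be narrowed. Some items come from the intake form, and the documents do not say whether the SF-12 is among them. It is therefore not established that the primary quality-of-life baseline is on treatment; the point holds for whichever items are collected directly.

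It may be said that handling of earlier members can be left to the analysis plan. A sensitivity analysis can be, but the protocol itself fixes a baseline definition that its own recruitment rule cannot meet for some participants.

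A reader might infer three stronger things that the documents do not support:

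- *That earlier members have had many months of care.* Neither the clinic's opening date nor any tenure is given, and the clinic is described as new.
- *That the cost pre-year is already treated.* This follows only from the one table cell.
- *That earlier members are survivors whose selection biases results in a known direction.* They must still attend after study start, but no attrition figure is given. A paired analysis also needs 12-month data from new members, so selection on retention is not peculiar to earlier ones.

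**Conclusion.** The point holds in two parts. The index date for the primary cost outcome is contradictory, and the choice matters only for members who joined before July 2013. If Table 1 were followed, the average effect would shrink by f·k/12: from 2.5% (f = 10%, k = 3) to 50% (f = 50%, k = 12) over the ranges assumed, given a constant effect from the first month. If clinic enrolment is followed, the loss is zero.

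Separately, and whichever cost anchor is used, self-report items collected directly from these members at study entry have a post-treatment baseline, which biases the uncontrolled baseline-to-12-month comparison. If benefit begins early, the bias is toward no change. Its size cannot be stated, because it depends on the number of earlier members, their tenure, the speed of any gain and which instruments are on the intake form, and the documents give none of these adequately.

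**What to change.** - Change the Table 1 cost row to clinic enrolment, and state in Data Collection that the comparators' average start date is the average clinic-enrolment date.
- Base the main self-report change analysis on members whose first UAIHC visit was on or after study start. Alternatively, include earlier members only for items with a genuine intake-form baseline, with follow-up timed from that date.
- Report earlier members' self-report results separately.
- Keep earlier members in the main cost analysis, with claims anchored at clinic enrolment, and add a new-patients-only sensitivity analysis. Dropping them from the main cost analysis is not justified once the anchor is corrected.

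The cost is a change of wording, a flag for joining date (already needed to define the claims window) and a somewhat smaller main self-report set. The documents do not allow that loss to be stated.
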